### 3.2.2 Safety

The objective of the study is to assess safety of NeuroAiD II™ (MLC901) compared to placebo, following a course of 6-month treatment in adult patients with long-term cognitive impairment after mTBI.

Safety outcomes will include:

1. Cumulative rate of treatment-emergent adverse events (TEAEs) and adverse drug reactions (ADRs) during the study;
2. Cumulative rate of SAEs during the study;
3. Discontinuation of treatment (for any reason or due to AEs);
4. Clinically significant (assessed by the Investigator) deviations in the results of hematology, blood chemistry and urine laboratory tests compared to baseline (Detailed in Section 4.1.1).

Study safety endpoints are detailed in Table 3.2.

Table 3.2. Study safety outcomes and endpoints

| Outcomes                                                                                                                        | Endpoints                                                                                                                                                                                                                                                                                                                            |
|---------------------------------------------------------------------------------------------------------------------------------|--------------------------------------------------------------------------------------------------------------------------------------------------------------------------------------------------------------------------------------------------------------------------------------------------------------------------------------|
| Cumulative rate of TEAEs and ADRs during the study                                                                              | 
 
Number of TEAEs, recorded during the study period (270±30 days) in the NeuroAiD II™ group and in the Placebo group
 
Number of ADRs, recorded during the study period (270±30 days, from Day 1 up to End-of-Study visit) in the NeuroAiD II™ group and in the Placebo group
 
 |
| Cumulative rate of SAEs during the study                                                                                        | Number of SAEs, recorded during the study period (270±30 days) in the NeuroAiD II™ group and in the Placebo group                                                                                                                                                                                                                    |
| Discontinuation of treatment (for any reason or due to AEs)                                                                     | Number of patients who discontinued treatment in the NeuroAiD II™ group and in the Placebo group 
 
Due to AE
 
For any reason
 
                                                                                                                                                 |
| Clinically significant deviations in the results of hematology, blood chemistry and urine laboratory tests compared to baseline | Number of clinically significant (assessed by the Investigator) deviations in the results of haematology, blood chemistry and urine laboratory tests upon NeuroAiD II™/Placebo treatment completion (Day 180±14) in the NeuroAiD II™ group and in the Placebo group compared to baseline                                             |

Safety assessment is detailed in Section 8.

## 4 STUDY DESIGN

### 4.1 Description of Study Design

This is a randomized double blind, placebo-controlled, multi-center clinical trial. The overview of the study design is given below in Figure 4.1. This clinical trial will include 182 adults (aged between 18 and 65 years of age) who experienced a mild TBI in the past 1 to 12 months and experience cognitive functioning difficulties as indicated by a score of >30 on the Cognitive Failures Questionnaire (consistent with criteria in the pilot study (21)). Eligible participants will be randomized to receive either NeuroAiD II™ (MLC901) or matching placebo.

The study will consist of 3 periods:

- **Screening** (Day -14..-1)
- **Treatment period** (6 months, Day 1 – Day 180±14), during which patients will daily receive an oral dose of IP or placebo
- **Follow-up period** (3 months, Day 180±14 – Day 270±30), after which final efficacy assessment will be performed

The time period from Screening (Visit 1) to Visit 2 (Day 1, Randomization) will not exceed 14 days. If the patient leaves the study before study completion for any reason, then the Early-Termination visit is performed, which should include all procedures and assessments, planned for the End-of-Study visit on Day 270±30.

[figure not shown]

Figure 4.1. Study design.

#### 4.1.1 Study procedures

##### Written Informed Consent

The Investigator will discuss all the necessary information about the study with the patient. The participant will have an opportunity to ask any questions about the study. Written consent must be obtained from all participants **prior to any study procedures**. The clinician/researcher obtaining consent should sign and date the consent form to state that the consent process has been completed according to the study protocol.

**Two copies of the consent form should be signed and dated.** One is to be retained by the participant. The other copy of the signed and dated information sheet and consent form must be left in the participant's file at the site.

The patient will receive the written information about:

- The investigational product and nature of this clinical study.
- Safety of the investigational product and risks for the patient.
- Terms of participation in the clinical study of the investigational product.
- Aim, objectives, and duration of the clinical study of the investigational product.
- Patient actions in case of unexpected effects of the investigational product on the patient's health.
- Terms of compulsory insurance of the patient's life and health.
- Confidentiality statement in relation to participation in the clinical study of the investigational product.

#### Screening procedure (Visit 1, Day -14..-1)

- The eligibility screening will include completion of the Cognitive Failures Questionnaire (CFQ). A score of >30 will be used to determine if the participant is experiencing cognitive impairment. CFQ will be performed after signing ICF at screening visit.
- If the subject has a CFQ score >30 and is ready to participate in the study, then the Investigator should check if the subject fulfils all other Inclusion and Exclusion Criteria.
- Collection of medical history, prior/concomitant medication (during the previous 12 months), demographic data (age, race), height, weight, BMI calculation, date/time of TBI and injury characteristics including worst recorded GCS score
- Pregnancy test
- Assessment of vital signs
- Physical examination
- Clinical Laboratory Tests
- ECG
- A meeting with the Investigator will be arranged for baseline assessment and randomization.

#### Randomization assessment (Visit 2, Day 1)

- Randomization
- Collection of baseline characteristics, medical history, prior/concomitant medication (Not necessary if complete information was obtained upon Screening)
- Efficacy outcomes to be assessed:
  - Cognitive functioning (complex attention, executive functioning, processing speed, memory (visual and verbal), reaction time) assessed with CNS-Vital Signs (CNS-VS)
  - Rivermead Post Concussion Symptoms Questionnaire (RPQ) - Questionnaire for Post-concussion symptoms
  - Health related quality of life (QOLIBRI) – Questionnaire for assessment of quality of life
  - Hospital Anxiety and Depression Scale (HADS) – Questionnaire for mood assessment
- Safety assessments:
  - Vital Signs
  - Physical examination
  - Collection of information about AEs
- Investigational product supply

#### Assessments after 1 and 3 months of treatment (Days 30±7 (Visit 3), 90±7 (Visit 4))

- Efficacy outcomes to be assessed:
  - CNS-Vital Signs (CNS-VS) - Computerized assessment for Cognition
  - Rivermead Post Concussion Symptoms Questionnaire (RPQ) -Questionnaire for assessment of post-concussion symptoms
  - Health related quality of life (QOLIBRI) – Questionnaire for assessment of quality of life
  - Hospital Anxiety and Depression Scale (HADS) – Questionnaire for mood assessment
- Safety assessments:
  - Vital Signs
  - Physical examination
  - Information about AEs
- Collection of prior/concomitant medication
- Compliance assessment
- Investigational product supply

Assessment after 6 months of treatment (Day 180±14, Visit 5)

- Efficacy outcomes to be assessed:
  - CNS-Vital Signs (CNS-VS) - Computerized assessment for Cognition
  - Rivermead Post Concussion Symptoms Questionnaire (RPQ) -Questionnaire for assessment of post-concussion symptoms
  - Health related quality of life (QOLIBRI) – Questionnaire for assessment of quality of life
  - Hospital Anxiety and Depression Scale (HADS) – Questionnaire for mood assessment
- Safety assessments:
  - Vital Signs
  - Laboratory tests
  - Physical examination
  - Information about AEs
  - ECG
  - Pregnancy test
- Collection of prior/concomitant medication
- Compliance assessment

Assessment 3 months after treatment completion (End-of-Study, Visit 6, Day 270±30)

- Efficacy outcomes to be assessed:
  - CNS-Vital Signs (CNS-VS) - Computerized assessment for Cognition
  - Rivermead Post Concussion Symptoms Questionnaire (RPQ) - Questionnaire for assessment of post-concussion symptoms
  - Health related quality of life (QOLIBRI) – Questionnaire for assessment of quality of life
  - Hospital Anxiety and Depression Scale (HADS) – Questionnaire for mood assessment

- Safety assessments:
  - Vital Signs
  - Physical examination
  - Information about AEs
- Collection of prior/concomitant medication
- Compliance assessment

Efficacy outcome assessments are detailed in Section 7. Safety outcome assessments are detailed below and in Section 8.

#### Laboratory tests

Standard hematology, blood biochemistry and urine tests will be conducted for safety monitoring at Screening (after eligibility is confirmed) and End-of-Study visits.

*Hematology* (approximately 5 mL blood sample):

- Haemoglobin (Hb)
- Hematocrit
- Total white blood cell and differential counts (Band cells and Segmented neutrophils, Eosinophils, Basophils, Monocytes, Lymphocytes)
- Red blood cell count
- Platelet count

*Blood chemistry* (approximately 5 mL blood sample):

- Total protein
- Aspartate Transaminase (AST)
- Alanine Transaminase (ALT)
- Glucose tests
- Creatinine
- Total Bilirubin
- Alkaline phosphatase

*Standard urine test:* specific gravity, color, pH, transparency, nitrites, glucose, protein, erythrocytes, epitheliocytes, cylinders, bacteria, leukocytes, mucus.

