## 2.4 Summary of the Known and Potential Risks and Benefits, if any, to Human Subjects

Risks to subjects in this study are related to:

- common procedures performed
- documented adverse events listed in the current reference products information.

These risks are communicated to the subjects in the consent forms.

Based on the safety profile of NeuroAiD II™, the risks through participating in the trial are considered low. Clinical safety data from MLC601 and MLC901 showed no overall increase in adverse events, most commonly reported AEs upon treatment were predominantly gastrointestinal, e.g. nausea, vomiting, diarrhea, and abdominal discomfort, which may be attributable to the number of capsules taken per day. The detailed list of expected events, that have been observed after IP administration in previous studies, is given in the respective section of IB (36).

Risks for subjects related to study procedures required by this protocol are minimal. The risk of participating in this clinical trial, similar to other trials, is related to blood drawing via venipuncture. Although hardly probable but there exists a possible risk of infection during blood sampling procedure. This risk can be eliminated by professionally performed procedure with qualified professional medical staff.

The total blood draw volume in this study is no more than 20 ml, which will be taken twice (in the beginning of the study and upon completion). Normal blood donation volume is up to 500 mL for one procedure, therefore the blood volume drawn in this study is incomparably lower than upon blood donation and there is no risk for volunteers in comparison to blood donation procedure.

The patients recruited in both NeuroAiD II™ and placebo are not in severe condition and are allowed to receive any other mTBI treatment besides IP. On the other hand, patients, receiving

placebo, avoid the risks, associated with IP intake and possible AEs, produced by its active substances.

Current study incorporates several measures to mitigate risks:

- measures will be taken during screening to ensure safety of the study subjects;
- the protocol specifies medical surveillance over the patients which includes recording and evaluation of AEs;
- in case of a known adverse reaction to the drug product, the investigator will take all the necessary actions, including discontinuation of the drug product;
- qualified personnel will perform the procedures in the scope of this study.

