#### 12-lead ECG

ECG will be done in supine position at Screening and End-of-study Visits. Subjects should be resting for at least 5 minutes prior to each ECG measurement.

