#### Pregnancy test (in women with childbearing potential)

Pregnancy test will be performed upon Screening and at Visit 5 (upon treatment completion). It will be a standard urine test for  $\beta$ -HCG (test strip).

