### 5.4 Subject Withdrawal Criteria

1. The patient withdraws the Informed Consent.

2. Patient's pregnancy: patients will be recommended to use effective contraception methods during the study, however if pregnancy occurs during the study, the IP/placebo treatment and other study procedures concerning the pregnant patient are cancelled, patient's pregnancy will be monitored up to pregnancy completion if the patient agrees.
3. Any medical condition of the patient that requires withdrawal of that patient from the study, as judged by the Investigator.
4. Patient lost to follow-up.

The investigator can withdraw a subject from the study if any of the withdrawal criteria are met. Patients are free to withdraw from the study at any time upon request, without any consequence. Patients should be listed as having withdrawn consent only when they no longer wish to participate in the study and no longer authorize the investigators to make efforts to continue collection of the outcomes. Every effort should be made to encourage patients to remain in the study for the duration of the planned outcome assessments. The patients should be told that their data are important for the scientific research, even after they discontinue the drug product.

The participant should no longer be contacted regarding the study after notification of withdrawal.

A subject will be considered lost to follow-up if he or she fails to appear for a follow-up assessment and cannot be contacted with good effort. These efforts will be documented in the subject's record. If not a single dose of the IP/comparator was taken by the patient, and he/she left the study for any reason, then further follow-up is cancelled, and his/her data are not included in the statistical analysis.

If the patient decides to leave the study or does not complete the study for any reason, then his randomization code should not be reused.

Unless the patient withdraws consent, those who discontinue the IP early remain in the study, if possible, for further collection of outcomes. The reason for discontinuation of the IP should be documented in the CRF.

The Investigator submits the data on the withdrawn patients to the Sponsor, local Principal Investigator and the monitor of the study within 24 hours in a report that includes the patient's status at the end of the study, as follows:

1. *Completed the study.*
2. *Did not complete the study because of:*

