### 8.2 Methods and Timing for Assessing, Recording, and Analyzing Safety Parameters

The corresponding safety endpoints are:

1. Number of TEAEs, recorded during the Study period (Day 1 – Day 270±30) in the NeuroAiD II™ group and in the Placebo group
2. Number of ADRs, recorded during the Study period (Day 1 – 270±30 days) in the NeuroAiD II™ group and in the Placebo group
3. Number of SAEs, recorded during the Study period (Day 1 – 270±30 days) in the NeuroAiD II™ group and in the Placebo group
4. Number of patients who discontinued treatment in the NeuroAiD II™ group and in the Placebo group
  - Due to AE
  - For any reason
5. Number of clinically significant (assessed by the Investigator) deviations in the results of haematology, blood chemistry and urine laboratory tests upon NeuroAiD II™/Placebo treatment completion (Day 180±14) in the NeuroAiD II™ group and in the Placebo group compared to baseline (data of laboratory tests and ECG performed at Screening)

At each study visit, the Investigator will ask patients about their well-being and assess whether any subjective AEs have occurred. The AEs, TEAEs, SAEs and ADRs will be recorded starting from the first IP dose intake (Day 1). Subjects may report to the Investigator the AEs occurring at any other time during the study. All subjects experiencing AEs, whether considered associated with the use of the study drug or not, must be monitored until resolution or stabilization.

Procedures for physical examination, vital signs assessment, 12-lead ECG and laboratory tests were detailed in Section 4. The physical examination results, as well as any changes that have occurred since the last inspection should be described in the primary documents and CRF. Data of physical examination, laboratory tests, vital signs and ECG data will be categorized as “normal”, “abnormal, clinically not significantly” or “clinically significant abnormal”. The clinically significant deviations in results of laboratory or instrumental assessment and physical examination data, vital signs and ECG data should be registered as AEs in eCRF.

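### Section 4.1.1 puts the safety laboratory tests and ECG at Day 270 although the schedule and endpoint use Day 180, and the schedule leaves the Early-Termination visit without either test

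*Protocol*

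**What the plan says.** Two procedure paragraphs in Protocol 4.1.1 set the timing of the safety tests. For the laboratory: "Standard hematology, blood biochemistry and urine tests will be conducted for safety monitoring at Screening (after eligibility is confirmed) and End-of-Study visits". For the ECG: "ECG will be done in supine position at Screening and End-of-study Visits". The visit lists in the same section define the End-of-Study visit: "Assessment 3 months after treatment completion (End-of-Study, Visit 6, Day 270±30".

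The rest of the protocol uses the earlier visit. Table 1.1 marks laboratory tests and ECG at Screening and Visit 5 and leaves Visit 6 blank. The synopsis and the visit lists in 4.1.1 agree with the table. The laboratory endpoint in 8.2 concerns haematology, "blood chemistry and urine laboratory tests upon NeuroAiD II™/Placebo treatment completion (Day 180±14"; the synopsis, Table 3.2 and 9.1.3 give the same time point. The pregnancy paragraph, directly after the ECG paragraph, uses Visit 5: "Pregnancy test will be performed upon Screening and at Visit 5 (upon treatment completion".

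On patients who leave early, 4.1 and the synopsis state that the "Early-Termination visit is performed, which should include all procedures and assessments, planned for the End-of-Study visit on Day 270±30". Stopping the drug is treated separately in 5.4: "Unless the patient withdraws consent, those who discontinue the IP early remain in the study, if possible, for further collection of outcomes".

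**The concern.** End-of-Study is a defined visit, so the two sentences cannot be read as loose wording for the end of treatment. Sections 3.2.2 and 8.1 also send the reader to 4.1.1 for the detail of the laboratory outcome, which is where the conflict lies.

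There are two consequences, and they are alternatives:

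- A site that follows the two sentences takes its only post-baseline laboratory sample and ECG about three months after treatment has ended, and has no Day 180 value for the stated laboratory endpoint.
- A site that follows Table 1.1 has the Day 180 result for everyone who attends Visit 5. A patient who leaves before then through an Early-Termination visit has no scheduled post-baseline laboratory test or ECG, because that visit is modelled on Visit 6.

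The laboratory endpoint covers haematology, chemistry and urine. For ECG the loss is of monitoring data, not of an endpoint.

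**Working it through.** **Statements of timing, side by side (all Protocol)**

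| Place | Laboratory tests | ECG |
|---|---|---|
| 4.1.1, procedure paragraphs | Screening, End-of-Study | Screening, End-of-Study |
| 1.3, Table 1.1 | Screening, Visit 5 | Screening, Visit 5 |
| Synopsis and 4.1.1, visit lists | Screening, Visit 5 | Screening, Visit 5 |
| Synopsis, Table 3.2, 8.2, 9.1.3 (endpoint) | Day 180±14 | not part of the endpoint |
| 4.1 and synopsis, Early Termination | as for Visit 6 | as for Visit 6 |

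The two procedure paragraphs are the outliers. Both sides of the conflict are current text, so this is not a difference from the amendment log.

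**Distance between the two timings.** Inputs: Visit 5 at Day 180±14 and Visit 6 at Day 270±30, taking the last dose to fall at Visit 5.

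- Nominal: 270 − 180 = 90 days.
- Shortest: (270 − 30) − (180 + 14) = 240 − 194 = 46 days.
- Longest: (270 + 30) − (180 − 14) = 300 − 166 = 134 days.

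**Could the conflict be met by testing at both visits?** Section 2.4 says: "The total blood draw volume in this study is no more than 20 ml, which will be taken twice". Section 4.1.1 gives about 5 mL for haematology and 5 mL for chemistry.

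- Two draws: 2 × (5 + 5) = 20 mL, which matches 2.4.
- Three draws: 3 × (5 + 5) = 30 mL, which exceeds it.

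Three planned draws therefore do not fit. Section 2.4 places the second draw at completion without saying whether of treatment or of the study, so it does not settle which visit is right.

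**Early Termination, reasoned through.** Under Table 1.1 no laboratory test or ECG falls between Screening and Visit 5, and none falls at Visit 6. The safety content of Visit 6 is vital signs, physical examination and adverse events. An Early-Termination visit copied from it contains no laboratory test or ECG. If the two procedure sentences governed instead, it would contain both. Correcting only those sentences would thus remove the one reading under which early leavers are tested.

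**Scale.** Inputs from 9.2: 182 randomized and a 30% dropout allowance.

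- Planned dropouts: 0.30 × 182 = 54.6. As a cross-check, 182 − 128 = 54.
- Leaving before Day 180 and attending an Early-Termination visit, at an assumed 25%, 50% or 75% of dropouts: 0.25 × 54.6 = 13.7; 0.50 × 54.6 = 27.3; 0.75 × 54.6 = 41.0.

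The protocol gives no figure for that share.

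**The case against.** The intended reading is easy to infer. Visit 5 is named in Table 1.1, the synopsis and the visit list directly above the faulty paragraphs, and the endpoint is fixed at Day 180±14. A site working visit by visit would probably test at Visit 5, and the likeliest departure is an extra sample at Visit 6, which leaves the endpoint intact. This stands as a judgement of likelihood. It does not make the two sentences correct.

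The Early-Termination point can be called a design recommendation, since the endpoint is tied to Day 180 and early leavers fall outside that time point. They are also not unmonitored: the visit keeps vital signs, physical examination and adverse events, and 5.6 and 8.4 follow events to resolution or stabilization. This stands in part. Neither section requires a laboratory panel or an ECG for a patient who leaves without symptoms.

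The numbers are soft. The 30% is a planning allowance, not a limit on actual dropout. Patients who stop the drug but remain can attend Visit 5, those lost to follow-up attend nothing, and 5.4 rules out further contact after notification of withdrawal. All of this is right: the true number is unknown, and 14 to 41 is only an illustration.

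Section 2.4 is a risk summary with approximate volumes, not a sampling schedule. Accepted, but it does speak against three planned draws.

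**Conclusion.** The concern holds. The laboratory and ECG sentences in 4.1.1 contradict the schedule, the visit lists and the laboratory endpoint. Followed literally, they move the only post-baseline test nominally 90 days past the last dose (46 to 134 days within the windows). Under the schedule that is evidently intended, patients who leave before Visit 5 have no scheduled post-baseline laboratory test or ECG. The size of that second gap cannot be fixed from the protocol. The illustration of 14 to 41 patients rests on the planned 30% dropout and on an assumed 25% to 75% share leaving before Day 180 and attending.

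The matter is limited to safety data. No formal safety testing is planned (9.1.3), no direction of bias is claimed, and the primary efficacy analysis and sample size are unaffected. It should be corrected because results not taken when a patient leaves cannot be recovered later.

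**What to change.** Make two changes together.

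1. In 4.1.1, let the laboratory and ECG paragraphs name Screening and Visit 5 (Day 180±14), as the pregnancy paragraph already does.
2. In 4.1, the synopsis and Table 1.1, state that an Early-Termination visit held before Visit 5 includes the Visit 5 laboratory tests and ECG.

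The cost is two corrected sentences, one Early-Termination rule carried into three places, the matching eCRF visit set-up, and the ethics committee approval that 11.4 requires for protocol revisions. Each early leaver who attends needs one local laboratory panel and one ECG. That draw replaces the Visit 5 draw, so the total stays at two draws and 20 mL, and 2.4 needs no change.
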